### Intervention strategy

The AMPLE program comprises four intervention arms:aCombination Group (FMS with cognitive challenge)A series of FMS games with cognitive challenges will be implemented by trained teachers during classroom time. Each game will last 30 min and will be played 3 times a week for a total of 3 weeks. An example of a game with cognitive challenges running as FMS training: “connect 4 real version”, a board with 7 columns and 6 rows, 1.2 m long and 1 m wide, will be placed, with all participants standing behind a taped line 15 m away and a timer set for 30 min. The goal of the participants is to place their 4 game pieces on the large board as quickly as possible and keep the pieces in a straight line (horizontal, vertical, or diagonal lines are all allowed). The game is played in pairs, and once a participant has placed their piece and run back behind the tape line, the next participant is allowed to begin [19]. Throughout the game, all participants will be monitored for heart rate to ensure that their heart rate is maintained within 65% to 85% of their maximum heart rate.bCognitive Group (Sedentary with cognitive challenge).A series of games with only cognitive challenges will be implemented by teachers during classroom time. Each game will last 30 min and will be played 3 times a week. An example of the game is “connect 4 routine version”, all participants will be seated at a table to ensure a sedentary state, and a timer will be set for 30 min. The goal of the game is to place 4 of their own game pieces on the board and try to connect the pieces in a straight line. The game is played in pairs, and once one participant has placed his or her piece, the other participant will be allowed to place the piece.cPhysical Group (FMS without cognitive challenge).A series of games with FMS interventions will be implemented by the teachers during classroom time. Each game will last 30 min and will be played 3 times a week. An example of the game is as follows: a clearly marked chart with rounds will be placed, all participants will stand behind a taped line 15 m away, and a timer will be set for 30 min. Once a participant has run out, they need to mark the number of rounds on the chart as soon as possible and return; once they have returned, the next participant is allowed to start and repeat. Throughout the game, all participants will be monitored for heart rate to ensure that their heart rate remains within 65% to 85% of their maximum heart rate.dControl Group (Sedentary without cognitive challenge).All participants will not engage in any cognitive challenge or FMS interventions but will sit in their own seats while the teacher plays a 30-minute story appropriate for young children. All participants will be informed prior to the start of the program that they will not be asked any questions related to the video or story and ensure a state of minimal cognitive engagement.

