The intervention period starts on October 20, 2025, and ends on July 12, 2026, lasting for 38 weeks (10 months). Kindergartens in Hong Kong have Christmas holidays in late December, traditional Chinese New Year holidays in mid-February, and summer vacations in mid-July. As a result, this study will put relatively long vacation periods in the washout period to ensure that all interventions and assessments could be completed in the kindergarten. In addition, in September, teachers may not be familiar with the newly enrolled children, and young children may not yet fully adapt to kindergarten life. Attrition is considered to appear during this period. Thus, the study will start in late October to ensure the smooth implementation of the intervention.

Data will be collected through a combination of objective measures and questionnaires and direct observation during the pre-test, post-test and follow-up test periods (see Fig. 1). In addition to professionally trained test evaluators, kindergarten principals and teachers will play an important role in the study. The principal will be the main contact person for the implementation of the study and will be responsible for approving and monitoring the full process of compliance with the program. Teachers in the relevant classrooms will be invited to participate in weekly workshops held by the research team until the end of the intervention. During the workshops, teachers will be carefully instructed on the carefully designed intervention plan for the following week for the different groups, dos and don’t, safety guidelines, etc., as well as how to use, fill out, and keep the evaluation booklet in between interventions. The attendance of all participating teachers will be recorded, which is considered to be one of the important factors that may affect the effectiveness of the intervention. Except for the kindergarten principal, teachers and children will be blinded to the differences in intervention strategies throughout the process, and all assessors will be blinded to group assignment. Unblinding will be permissible after the end of the project.

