#### Measurement of social competence

The Social Competence and Behavior Evaluation Scale (SCBE-30) will be used to assess the social competence of young children [65]. The scale is divided into three domains: social competence (including joyful, secure, tolerant, socially integrated, calm, prosocial, cooperative, and autonomous); anger aggression (including angry, aggressive, egotistical, and oppositional); and anxiety withdrawal (including depressed, anxious, isolated, and dependent). There are 30 items in total, using a 6-point Likert-style scoring, with 1 representing “never” and 6 representing “always”. Several previous studies have verified that it has good reliability among children in different countries [66–68], especially in assessments of over 1400 Chinese children aged 3–6 years (α = 0.66–0.92) [69, 70]. The scale will be completed independently by teachers and parents before and after the intervention, with the assessment of inter-rater reliability.

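### Teachers and children are declared blind to the intervention differences, but teachers learn and deliver all four conditions and also rate the social-competence outcome behind H4

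*Protocol article*

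**What the plan says.** The blinding statement is in the protocol article under Data collection procedures. With the principal as the only exception, "teachers and children will be blinded to the differences in intervention strategies throughout the process", and in the same sentence "all assessors will be blinded to group assignment".

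Earlier in the same paragraph, on the weekly workshops, "teachers will be carefully instructed on the carefully designed intervention plan for the following week for the different groups".

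Under Intervention strategy, teachers run each of the game conditions:
- combination: "A series of FMS games with cognitive challenges will be implemented by trained teachers during classroom time"
- cognitive: "A series of games with only cognitive challenges will be implemented by teachers during classroom time"
- physical: "A series of games with FMS interventions will be implemented by the teachers during classroom time"

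In the control condition the teacher plays a story while the children stay seated.

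Under Measurement of social competence, on the SCBE-30: "The scale will be completed independently by teachers and parents before and after the intervention". An assessment of inter-rater reliability is added. No other social-competence instrument is named, so this scale carries H4 (Background), which predicts larger gains with intervention than control and the largest in the combination group.

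**The concern.** A stated design property is one the design cannot have. Someone who is taught four programmes and then runs them knows how they differ.

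For the outcomes measured by separate trained evaluators, this matters less as long as those evaluators are kept masked. It matters directly for the SCBE-30, a subjective 6-point rating that teachers help to supply. A reader who takes the blinding statement at face value would treat the teacher ratings as protected from expectation. They are not, and a difference between conditions on the teacher score could reflect what teachers expect as well as what children do. At stake is how much weight an H4 result can bear.

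**Working it through.** The protocol gives no figure on this point and no arithmetic applies. The check is whether the statements can be true together.

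**Step 1: what teachers know.**

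| Section of the protocol article | What it establishes |
|---|---|
| Data collection procedures | Teachers are said to be blind to how the strategies differ |
| Data collection procedures (same paragraph) | Teachers receive each coming week's plan for the different groups |
| Randomization | Teachers are sent material on the theory behind the study, its aims and its methods |
| Intervention strategy | Teachers deliver the three game conditions and the story control |
| Strengths and potential limitations | Delivering four programmes accurately over 10 months is named as a fidelity challenge for teachers |
| Patient and public involvement | Teachers take part in early discussions while the protocol is developed and give feedback on delivery throughout |

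The first row cannot stand beside the others. A weaker meaning, that teachers know the activities but not the reasoning behind them, is not what the sentence says, and the material sent to teachers undercuts it as well.

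**Step 2: what children know.** The Fig. 2 caption (Timeline) has every cluster receive all four conditions in turn. Running to a board 15 m away, sitting at a board game and listening to a story are different to anyone doing them. Control children are also told beforehand that no questions will follow. Children aged 3–5 may not grasp the purpose of the study, but they are not unaware that the sessions differ.

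**Step 3: which outcome is exposed.** Teachers and parents complete the SCBE-30, and H4 has no other named measure. The teacher score is therefore an unblinded rating that serves H4. Because parents also rate the scale, H4 depends on unblinded teachers only in part.

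**Step 4: does the crossover remove the problem?** Write the expected teacher rating of a class under condition c as

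E(rating) = class and teacher level + period effect + τ_c + δ_c,

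where τ_c is the true effect of the condition and δ_c is any shift in rating due to what the teacher expects of it. After adjustment for period, the within-class contrast of conditions a and b is

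(τ_a − τ_b) + (δ_a − δ_b).

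The class and teacher level cancels, which is the advantage claimed under Strengths and potential limitations. The δ terms do not cancel unless teachers expect the same of both conditions.

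**Step 5: does the reliability check remove it?** Inter-rater reliability describes how well teachers and parents agree. Good agreement would not show that either score is free of expectation, and poor agreement would not show which score is affected. The check corrects neither score.

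**Step 6: size.** A numerical bias or false-positive rate would need δ and the standard error of an SCBE-30 contrast. The article gives no expected shift, no SD for the scale, no intraclass or cluster-period correlation and no within-child correlation.

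**The case against.** The contradiction over teachers has no good answer, but several stronger readings that a reader might infer go further than the document.

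- **That the statement about assessors is also false.** Data collection procedures mentions trained evaluators separately from teachers, and the shuttle-run description uses the word assessor for the adult who runs with the children. The assessor clause may cover only such people. For questionnaire raters it is ambiguous, not shown to be untrue. This does not rescue the teacher claim, because teachers are called blind in their own right.
- **That each teacher rates the class to which he or she delivered the condition.** This is likely, since no other rating teachers are mentioned, but the article does not say so.
- **That expectation follows condition exactly.** Knowledge of the condition is certain. What teachers expect about social competence, and how strongly, is not documented. What is established is a risk of bias, not a bias of known direction.
- **That a false-positive rate can be attached.** Any such figure would rest on an assumed bias and an assumed standard error, so none is given here.
- **That the article is deficient for not naming the rater who decides H4.** The choice between two informants is commonly left to the full protocol or analysis plan, which is not shown.
- **That the parent score is a blind substitute.** Parents receive the research objectives and timetables (Randomization), and children can describe the sessions at home. Parents do not deliver the conditions and are less exposed, but no more than that can be said.

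The remaining defence is that a journal article condenses a fuller protocol. It does not apply here: this is an affirmative statement contradicted by the same article, not an omitted detail.

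**Conclusion.** The concern holds. Teachers and children cannot be blind to the differences between the strategies under the design described. The teacher-rated SCBE-30 is therefore an unblinded outcome open to expectation bias that can change with condition and that neither the crossover nor the reliability check removes. The size and direction of that bias cannot be derived from the document.

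The effect on conclusions shown here is confined to one of five hypotheses, and within it to one of two informants. It is worth correcting before results are reported, but it does not undermine the trial as a whole. The conclusion on H4 assumes that the teachers who complete the scale are among those trained in or delivering the conditions, which the article implies without stating.

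**What to change.** 1. Under Data collection procedures, delete the claim that teachers and children are blinded and say plainly that they are not.
2. Limit the blinding statement to the independent trained test evaluators.
3. Under Measurement of social competence, state that teacher and parent SCBE-30 scores will be analysed and reported separately and not pooled, and label the teacher score as unblinded.
4. State that no claim on H4 will be based on the teacher score alone.
5. Describe the parent score as the less exposed of the two, with at best partial masking. Making it the sole deciding endpoint is an option that the trial team may prefer, but the correction does not depend on it.

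Both ratings are already planned, so the cost is a change of wording and a separate presentation of two scores. The downside is a somewhat more cautious conclusion on H4.

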**Fig. 1 Fig1:**
[figure not shown]
Flow diagram of participants’ progress through different phases. *Abbreviations*. *CC * Cognitive Challenge, *CRF *Cardiorespiratory Fitness, *EF * Executive Function, *EmQue * Empathy Questionnaire, *FMS * Fundamental Movement Skills, *PA * Physical Activity, *RPE * Rating of Perceived Exertion, *RPME * Rating of Perceived Mental Exertion, *SCBE * Social Competence and Behavior Evaluation Scale

### Outcome measures

#### Measurement of physically related outcomes

##### Cardiorespiratory fitness (CRF)

The original version of the 20 m shuttle-run test (20mSRT) has been widely used to assess the cardiorespiratory fitness of a cumulative total of more than 1 million children and adolescents worldwide and has been found to be strongly correlated with maximal oxygen uptake [48]. However, its original protocol, which commences at a speed of 8.5 km·h⁻¹, is unsuitable for preschoolers aged 3–5 years, as the high initial intensity can impede performance and compromise test reliability and feasibility. Consequently, some young participants are unable to complete a single shuttle, leading to significant deviations between estimated and actual fitness levels [49].

To address this limitation, this study employs the 20mSRT-PREFIT (20 m shuttle-run test PREschoolers FITness assessment), an adapted protocol developed specifically for this age group [50]. This version modifies the test by reducing the initial speed to 6.5 km·h⁻¹ and incorporates the presence of an adult assessor who runs alongside the children to ensure safety and procedural continuity [51, 52]. CRF has been measured in more than 3,000 preschool children via the 20mSRT-PREFIT, and this protocol demonstrated high reliability (α = 0.833, *p* < 0.01) and greater discrimination compared to the original version in a previous assessment of cardiorespiratory fitness in young children aged 4–6 years [50, 53].

The test requires participants to run from one marked line to another marked line 20 m apart and to run back and forth continuously until exhaustion. They were alerted to this process by an audio signal of progressively increasing speed, set at an initial speed of 6.5 km h^− 1^, which would increase at a rate of 0.5 km h^− 1^ per minute. The test will be stopped when the participant fails twice to reach the marker line at the time of the audio signal or is unable to continue due to fatigue. Later in the test, the participants will be continually encouraged to continue persevering so that their best performance can be recorded. The manual of implementation within video and audio on how to perform and score the 20mSRT-PREFIT is available on the website from the PROFIT Research Group (http://profith.ugr.es/recursos-prefit).

##### Fundamental movement skills (FMS)

The Test of Gross Motor Development Third Edition (TGMD-3) will be used to test participants’ FMS, which is specifically designed for children aged 3–10 years. As a procedure-oriented assessment test tool, it can evaluate the specific performance and completion process of children’s movements, and the operation process is simple and easy to observe. Therefore, it is widely used in the assessment of children’s FMS. TGMD-3 consists of a locomotor skills test and an object control skills test, which together have 13 movements (run, gallop, hop, skip, jump, slide, two-handed strike, one-handed strike, dribble, catch, kick, overhand throw, and underhand throw). The participants will be asked to watch a skill demonstration and be allowed to take a practice test before completing two formal tests. Proficiency the test will be assessed, with 3–5 movement criteria for each move. If a performance criterion for a skill is met, a score of “1” is given; if it is not met, the score is “0”. Each item will be tested twice, and the score will be accumulated for each item. The maximum total original score for the locomotor skill subscale is 46 points, and the maximum score for the object control skill subscale is 54 points. The higher the score is, the better the performance [54]. The assessments will be videotaped and scored by trained professionals [55].

Since the TGMD-3 does not include the assessment of stability skills in young children, the stability skill test (SST) will be used [56]. This test has been used for the assessment of 556 young children and was found to be a reliable scale (α = 0.81) [57]. The SST consists of three parts (rock, log roll and back support), and there are also 3–5 criteria for each move, with each movement tested twice. The final score of the two tests will be added to obtain the final score of the stability skill. The higher the score is, the better the stability skill [56].

#### Measurement of physical activity

PA levels will be assessed via an accelerometer (GT3X+, Actigraph, Florida, USA). This accelerometer is widely utilized in the assessment of PA in children and adolescents and has been shown to be equally effective in young children aged 3–6 years [58]. The participants in this study will be asked to wear the accelerometer for at least 8 h per day for 6 consecutive days, and their PA levels will be categorized as sedentary, light, moderate, or vigorous.

#### Measurement of executive function

##### Working memory (WM)

Working memory will be assessed via the word list recall test (WLR), which is a subset of the children’s working memory test battery and requires participants to memorize and recall word sequences and verbally retell them at specified intervals. As a simple working memory task, participants only need to memorize and repeat the words in the correct pronunciation and sequence without additional manipulation or processing, making it a simple and effective working memory test. Previous assessments using the WLR with preschoolers have demonstrated good retest reliability (α = 0.72–0.8) [59, 60]. In the present study, young children will first hear 2 words that they can understand, and after successfully repeating them with the correct pronunciation and sequence, will add 1 word and repeat the previous maneuver, stopping until two occurrences of an inability to repeat the word or sequence. The number of words that can be recalled accurately will be recorded.

##### Cognitive flexibility & inhibitory control

The Trial Making Test for Preschoolers (TRAILS-P) consists of 4 conditioned tests, with Conditioned Test B being used to assess cognitive flexibility and Conditioned Test C being used to assess inhibitory control. Good reliability (α = 0.64) has been demonstrated in studies with over 100 preschoolers [9, 61]. In Conditional Test B, children will be required to match five dogs and five corresponding bones by stepping on them. In Conditional Test C, the bones serve as distractors, and young children will be required to accurately stamp 10 dogs in order from smallest to largest and to ignore the five interspersed bones. The time taken by the child to complete the task and the number of errors made during the test will be recorded.

#### Measurement of affective/emotional competence

The children’s emotional competence was assessed via the Empathy Questionnaire (EmQue) [62]. The scale was constructed on the basis of the widely accepted Hoffman empathy theory [63] and is divided into three domains: emotion contagion (i.e., being able to pay attention to others’ emotions but not be able to distinguish the subject of the emotion, e.g., My child also needs to be comforted when another child is in pain); attention to others’ feelings (i.e., being able to perceive others’ emotions and distinguish the subject of the emotion, e.g., when an adult becomes angry with another child, my child watches attentively); and prosocial actions (i.e., being able to perceive and distinguish the subject of the emotion and intervene in others, including helping, sharing, and comforting, e.g., when I make clear that I want some peace and quiet, my child tries not to bother me). The 20-item scale uses a 3-point rating scale (0 = never; 1 = sometimes; 2 = often) to assess the child’s behavior over the past two months. It has shown acceptable reliability (α = 0.58–0.81) in previous studies of parents and is significantly predictive of emotion regulation ability [62, 64]. The scale will be completed independently by parents before and after the intervention.

#### Measurement of social competence

The Social Competence and Behavior Evaluation Scale (SCBE-30) will be used to assess the social competence of young children [65]. The scale is divided into three domains: social competence (including joyful, secure, tolerant, socially integrated, calm, prosocial, cooperative, and autonomous); anger aggression (including angry, aggressive, egotistical, and oppositional); and anxiety withdrawal (including depressed, anxious, isolated, and dependent). There are 30 items in total, using a 6-point Likert-style scoring, with 1 representing “never” and 6 representing “always”. Several previous studies have verified that it has good reliability among children in different countries [66–68], especially in assessments of over 1400 Chinese children aged 3–6 years (α = 0.66–0.92) [69, 70]. The scale will be completed independently by teachers and parents before and after the intervention, with the assessment of inter-rater reliability.

